### Statistical analysis

Survey data will be stored on the password-protected, user-authenticated encrypted computer hard drive. Before conducting analyses to address the aims, preliminary analyses will be conducted to evaluate the quality of data and to fix illegal values.

*Aim 1 will compare effectiveness of two interventions* (community-based interactive youth educational program and community-based interactive youth educational program plus Internet booster) *to the no-intervention control treatment.* A secondary component of Aim 1 is to compare two interactive hearing interventions on youth.

The primary measure to assess effectiveness is the 6 item scale of intention to use hearing conservation strategies (including turning down the volume, moving away from the noise, and using hearing protection devices such as ear plugs). The knowledge scale and the scale of interpersonal influences will also be examined. All individuals will be asked to assess these measures before intervention (baseline), and at 3 months and 12 months after the intervention. Since the cluster randomized design will be used to assign interventions and repeated measurements will be collected from the same individuals, linear mixed effects model will be used to investigate the effect of the interventions. The outcome variable is the scale of intention to use hearing conservation strategies. The important/main fixed effect is a categorical variable identifying the type of interventions. In addition, demographics variables will be included in the mixed model as fixed effects to increase the precision of estimates. The random effect in the model is the *site* variable. More precisely, we will use random intercept model for the *site* variable. We assume the site variable follows a normal distribution with mean zero and is independent to the error terms in the mixed model. The hypothesis is that there will be a significant effect of hearing intervention on the use of hearing conservation strategies and the intervention group will have higher use of hearing conservation strategies than the control group. If the effect of intervention is significant, follow up descriptive statistics on mean intent by time by treatment group will allow us to describe the effects, for example to determine whether each treatment led to more improvement in intent to use than the control condition and how big those effects were. Further tests within this analysis will compare the effects of the two interactive hearing interventions on youth.

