**Methods:**

The purpose of this project is to test innovative hearing health education programs delivered to a large target group and to determine the effectiveness and sustainability of these programs in promoting hearing health among farm and rural youth. Specifically, this project includes: a) an interactive face-to-face informational program alone, b) an interactive face-to-face informational program followed by an Internet-based booster, and c) a no-intervention control. Sites will include selected affiliates of a major farm youth safety education organization. Data will be collected at baseline, 3, and 12 months. A linear mixed model will be used to compare the effectiveness of the three interventions over time. Descriptive statistics will be used to compare program costs and sustainability ratings.

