### Power and sample size justification

The sample size, in particular the number of sites, was determined by power analysis for a mixed model design using Optimal Design software [39]. The number of sites was selected to provide 80 % power to detect an effect of either intervention with effect size *d* of .48 compared to the effect of the control treatment. This is the effect size on intention to use hearing conservation strategies we found in our preliminary study and is just under what Cohen defined as a medium sized effect. Other necessary inputs into Optimal Design were ranges of the average number of students per site and estimates of the intraclass correlation coefficient (ICC), a measure of the tendency of individuals in the same site to have similar (correlated) responses. To determine the number of sites needed, we examined numbers of site ranging from 20 to 80, and a value of the ICC of .10 (which is typical of its value in health education intervention research [40]. We also adjusted for the possibility of 20 % missing posttest data (which we did by reducing the number of individuals per site by that percentage: thus actually testing the number of individuals per site from 16 to 64). These last adjustments increased the number of clusters we needed to include. The result of the power analysis was 80 % power to detect the target effect size with alpha of .05 two tailed if we included 36 sites with an average 16 individuals per site. Thus we have designed the study to include 36 sites (divided equally among the 3 treatments). Assuming each site includes more than 16 individuals, we will have more than 80 % power. Target youth enrollment of 576 is based on these calculations and US Agriculture Census data [41]. Enrollment numbers also include coordinators (n = 36) and instructors (n = 24).

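### As written, the primary model tests an intervention effect averaged over baseline and both follow-ups, which dilutes the effect the trial was powered to detect

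*Protocol article*

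**What the plan says.** The Statistical analysis section (Aim 1) gives the measurement schedule: "All individuals will be asked to assess these measures before intervention (baseline), and at 3 months and 12 months after the intervention". It cites the repeated measurements, together with cluster randomization, as the reason for a linear mixed model. On the fixed effects it states: "The important/main fixed effect is a categorical variable identifying the type of interventions". Demographic variables are added for precision, and the random part is a normally distributed site intercept. The hypothesis is a significant effect of intervention.

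Time appears in this analysis only after that effect is significant: "follow up descriptive statistics on mean intent by time by treatment group will allow us to describe the effects". The example given is to determine whether each program improved intent more than control did.

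Two other places bear on this. The Abstract says: "A linear mixed model will be used to compare the effectiveness of the three interventions over time". The Power and sample size justification says: "The number of sites was selected to provide 80 % power to detect an effect of either intervention", with a d "of .48 compared to the effect of the control treatment".

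**The concern.** A main effect of intervention over three waves is the arm difference averaged over those waves. Randomization makes the expected difference at baseline zero, so including that wave pulls the tested effect toward zero. The question of interest, whether a program raises intention after it is delivered, is left to a comparison of means by time and arm.

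At stake is a primary test with well under its advertised power, which could miss a program that works as well as the pilot suggested. There are two knock-on effects. The cost-effectiveness ratio in Aim 2 is calculated only if the effect is significant. The comparison of the two programs suffers most: the booster is delivered after the 3-month survey, so a booster effect δ sits in one wave of three and enters the averaged term as δ/3.

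**Working it through.** **Inputs from the article.** 36 sites in three equal arms, so 12 per arm; m = 16 youth per site; ICC .10; d = .48; the power claim is "power to detect the target effect size with alpha of .05 two tailed". There are three waves, one of them before the intervention, and the site intercept is constant over waves.

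**Assumed, because the article does not give them.** r is the correlation between waves within a child, net of site, taken as .3 to .7. s is the share of site variance that persists across waves; s = 1 is the article's own model and lower values are sensitivity checks. Total variance is 1.

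**1. Reproduce the stated power.** For one post-test comparison of one program with control:

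- variance of a site mean = .10 + .90/16 = .15625
- SE = √(2 × .15625/12) = .1614
- .48/.1614 = 2.97; noncentral t with 22 df gives 81%

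So the stated 80% matches a pairwise comparison at a single post-intervention wave, with the full .48.

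**2. Expected value of the term as written.** (0 + .48 + .48)/3 = .32. A time main effect shifts all arms equally, so with balanced waves the arm difference is still this average. Adding only that term does not remove the dilution.

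**3. Power of the term as written.** Variance of a site's three-wave mean = .10(1 + 2s)/3 + .90(1 + 2r)/(3 × 16). For s = 1 and r = .5 this is .10 + .0375 = .1375; SE = √(2 × .1375/12) = .1514; .32/.1514 = 2.11; power 52%. The full grid (22 df):

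| s | r = .3 | r = .5 | r = .7 |
|---|---|---|---|
| 1 (article's model) | 55% | 52% | 50% |
| .8 | 59% | 57% | 54% |
| .5 | 67% | 64% | 61% |
| .2 | 77% | 73% | 70% |
| 0 | 85% | 80% | 76% |

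Using 33 df (36 sites minus 3 arms) adds about one point; the largest value at s = .5 becomes 69%. A simulation of the written model at r = .5 (4,000 runs) gave 54%, 58% and 66% for s = 1, .8 and .5. With 20% loss from 16 (m = 12.8), the first row falls to about 48-52%.

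**4. Power with the pre-intervention wave taken out of the effect.** The unadjusted average of the two follow-ups keeps the full .48. At s = 1 and r = .5 its site-mean variance is .10 + .90 × 1.5/32 = .1422, SE .1539, power 85%.

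For the 12-month contrast adjusted for baseline, the variance is .15625(1 − ρ²), where ρ = (.10s + .90r/16)/.15625:

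- s = .5, r = .3 (lowest cell with s ≥ .5): ρ = .428, SE .1458, power 88%
- s = 1, r = .3: ρ = .748, SE .1071, power 99%
- m = 12.8, s = .5, r = .3: SE .1531, power 85%
- m = 12.8, s = .2, r = .3: SE .1635, power 80%

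**5. Departures from the equal-effect, complete-data case.** In general the term is (d at 3 months + d at 12 months)/3. If 20% of post-tests were missing and not imputed, it would be .48 × 1.6/2.6 = .295, a fall of about 38%; the article does plan multiple imputation. Table 2 lists 3-month surveys for Groups A and B only, and the Retention section makes the number of surveys depend on arm. If controls have no 3-month score, a model without time would also mix any general trend into the arm difference.

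**The case against.** The strongest reply is that a journal article condenses. Naming the main fixed effect and adding demographics does not say that the list is exhaustive. The Abstract speaks of comparison over time, and nothing says outright that baseline is analysed as a response. That is fair: the article does not show that the team has ruled out a time term or baseline adjustment. But it does more than stay silent. It names the effect to be tested and gives time a descriptive role. The Abstract's wording conflicts with this and names no term that would settle it.

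A reader might infer that the comparisons of each program with control get no model-based test or interval. The article does not support that. A three-level fixed effect yields A-versus-C and B-versus-C coefficients with standard errors, Aim 1 states those comparisons, and further tests are promised for A versus B. The defect is that these coefficients carry the same dilution. Nor does the article make raw means the only decision rule; they follow a significant test, although the wording about determining whether each program did better is loose.

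A reader might also take the one-third shrinkage and the loss of power as unconditional. They are not. The booster's timing makes an unequal effect in Group B plausible, and with little site persistence (s = .2 or less) the written test has roughly 70-85% power. There the gain from the remedy is small, and at s = 0 with low r there is none. That situation departs from the constant site intercept the article itself specifies.

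**Conclusion.** The point holds for the analysis as written. The tested term mixes a pre-intervention wave into the effect, and the power statement belongs to a different comparison. With d = .48 at both follow-ups, no systematic baseline difference and complete waves, the tested effect is .32. Under the article's site model its power is about 50-55%, against the stated 80%. The range widens to about 69% if half the site variance is wave-specific. The within-child correlation and the persistence of site effects are assumptions; the reduction to .32 does not depend on them.

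The documents do not support going further and calling 12 months the only correct primary time point. None is named, and choosing between 12 months and the post-intervention average is for the sponsor.

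**What to change.** In the Statistical analysis section (Aim 1):

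- Enter baseline intention as a covariate, or constrain arm means to be equal at baseline.
- Include time and intervention-by-time as fixed effects.
- Name the post-intervention target, either 12 months or the average of the follow-ups. Base the A-versus-C and B-versus-C conclusions on model contrasts at that target, each with a 95% CI. Keep the means by time and arm as description only.
- State whether controls are surveyed at 3 months, and reconcile this with Table 2 and the Retention section.

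The cost is analysis wording; baseline scores are already collected and no added sites or youth are needed. When at least half the site variance persists, the baseline-adjusted 12-month contrast has about 88% power or more with 16 complete youth per site, and about 85% or more with 12.8.

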Intervention B consists of an Internet-based educational booster. The Internet-based booster reinforces Intervention A content through use of the Dangerous Decibels® virtual exhibit (DDVE), an existing online educational program consisting of eight activities (www.dangerousdecibels.org/exhibit/virtual-exhibit/). The booster is developmentally appropriate, focuses on sources of sounds, consequences of noise exposure, and prevention of hearing loss. In a study testing the effectiveness of the DDVE site when used alone, students showed improvement in knowledge immediately after the intervention, although improvements were not sustained after 3 months. The Internet-based booster is a user-driven activity where students explore a variety of learning activities at their own pace. Highly interactive game-based activities include rating noise sources (e.g., lawn mower) as safe or dangerous, determining the best course of action (i.e., turn it down, walk away, wear hearing protection) in a variety of noisy situations, and choosing a course of action when confronted with social non-support of use of hearing protection. A computer (with Macromedia Flash® and Shockwave®) and Internet connection (e.g., at home, school, or public library) is required for participation.

The study design includes three arms: an interactive a face-to-face Safety Day lesson alone (Group A), a face-to-face interactive lesson followed by an Internet-based booster (Group B), and a no-invention control (Group C, Fig. 2). The Internet booster will be delivered to eligible participants following completion of the three month survey.

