#### Intervention effectiveness evaluation

After obtaining parental informed consent and soliciting the assent of child participants, pre- and post-intervention data will be collected from youths. Pre-test data will be collected via pencil-and-paper survey forms prior to the delivery of content. Three- and 12-month post-test data will be collected via the youth’s preferred communication medium following the booster intervention. Instrument means, standard deviations, and alpha coefficients are summarized in Table 2.

**Table 2 Tab2:** Timetable of project activities and benchmarks for success

Activity	Year 1 months						Year 2 months						Year 3 months						Year 4 months		
	1/2	3/4	5/6	7/8	9/10	11/12	13/14	15/16	17/18	19/20	21/22	23/24	25/26	27/28	29/30	31/32	33/34	35/36	37/38	39/40	41/42
Recruit, enroll & randomize 36 sites	X	X	X	X																	
Train coordinators (Groups A,B); & distribute materials (Groups A,B,C)		X	X	X	X	X															
Recruit 24 instructors; enroll youth; collect baseline data; deliver interactive program (Groups A,B)					X	X	X	X													
Distribute, collect 3-month surveys (Groups A,B)					X	X	X	X	X	X											
Distribute booster reminders (Group B)							X	X	X	X	X	X									
Collect 12-month surveys; distribute incentives (Groups A,B,C)											X	X	X	X	X	X					
Complete sustainability assessment														X							
Analyze data															X	X	X				
Submit progress reports						X						X						X			X
Disseminate & submit manuscripts																			X	X	X

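### With no time-by-arm term, the stated model averages Group B's pre-booster and post-booster scores and makes no use of Groups A and B being the same at 3 months

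*Protocol article*

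**What the plan says.** **Arms and timing.** The Interventions section defines Group A as the lesson alone, Group B as "a face-to-face interactive lesson followed by an Internet-based booster (Group B"), and Group C as no intervention. It then states: "The Internet booster will be delivered to eligible participants following completion of the three month survey".

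**Model.** The Statistical analysis section applies a linear mixed model to the intention scale. Its treatment term is described as follows: "The important/main fixed effect is a categorical variable identifying the type of interventions". Demographics are further fixed effects. On the random part it says: "More precisely, we will use random intercept model for the *site* variable". Time by group appears only in descriptive summaries that follow a significant intervention effect. The booster question is left to one sentence: "Further tests within this analysis will compare the effects of the two interactive hearing interventions on youth".

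**Statements that conflict.**

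| Point | One place | Another place |
|---|---|---|
| Booster and the 3-month survey | Interventions: booster after the survey | Intervention effectiveness evaluation: "Three- and 12-month post-test data will be collected via the youth’s preferred communication medium following the booster intervention" |
| Group C at 3 months | Statistical analysis: "All individuals will be asked to assess these measures before intervention (baseline), and at 3 months and 12 months after the intervention" | Table 2 timetable: "Distribute, collect 3-month surveys (Groups A,B"), with all three groups listed for the 12-month survey. The Retention section also says that the number of surveys depends on study arm. |

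**The concern.** On the order given in the Interventions section, the true B-versus-A difference is zero at 3 months by design, and any booster effect can appear only at 12 months. A term that is constant over time cannot represent that pattern. It reports a mixture of a comparison in which nothing differs and a comparison in which the booster differs. The comparison of the two programs is a stated secondary component of Aim 1, and the Background presents the booster as the under-tested element, so this dilution falls on a question the trial was set up to answer.

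The same design fact offers two things that the stated model does not use. The 3-month score is a ready pre-booster value for B versus A. And if Group C is surveyed at 3 months, 24 sites rather than 12 inform the effect of the lesson at that time.

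**Working it through.** **Inputs (Power and sample size justification):** 36 sites, 12 per arm; 16 youth per site; ICC .10; d = .48; two-sided alpha .05. The 3-to-12-month correlation of site means, r, is not given. It is an assumption and is shown over a range. Equal variance at the two follow-ups is also assumed.

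**1. The plan's own figure.** Variance of a site mean in SD units: v = .10 + .90/16 = .15625. For 12 v 12 sites, SE = √(.15625 × 2/12) = 0.161. The noncentral t with 22 df gives 81.1% power at d = .48, which reproduces the stated 80% as a pairwise comparison with control. The effect detectable with 80% power is 0.473.

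**2. Dilution of B versus A.** Let δ be the booster effect at 12 months; at 3 months it is 0. A time-constant term with equal weight on the two follow-ups estimates (0 + δ)/2 = δ/2. If baseline scores also enter as responses under the same constant term, it is (0 + 0 + δ)/3 = δ/3.

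For the two-follow-up case, the variance of the averaged site mean is v(1 + r)/2. The 12-month booster effect detectable with 80% power is then 2 × 0.473 × √((1 + r)/2):

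- r = .3: 2 × 0.473 × 0.806 = 0.76
- r = .5: 2 × 0.473 × 0.866 = 0.82
- r = .7: 2 × 0.473 × 0.922 = 0.87

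A plain 12-month comparison of B with A, 12 v 12 sites, detects 0.47.

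**3. The 3-month score as pre-booster value.** Conditioning on it multiplies the variance of the 12-month B-versus-A contrast by (1 − r²), with 21 df:

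| r (assumed) | Variance cut | Detectable effect |
|---|---|---|
| 0 | 0% | 0.47 |
| .3 | 9% | 0.45 |
| .5 | 25% | 0.41 |
| .7 | 49% | 0.34 |
| .8 | 64% | 0.28 |

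The comparator here is an unadjusted 12-month difference. Whatever the pre-lesson baseline already explains must be taken off the gain.

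**4. The lesson effect at 3 months, if Group C is surveyed then.** For 24 v 12 sites, SE = √(.15625 × (1/24 + 1/12)) = √(.15625 × .125) = 0.140. The variance ratio to A versus C is .125/.1667 = 0.75, a cut of 25%. Power at d = .48 with 34 df is 91.6%, and the detectable effect falls from 0.473 to 0.403. If 16 per site is the number enrolled and 20% are lost (12.8 left), power goes from 77.7% to 89.2%.

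**5. Does the three-level factor itself lose this?** Write w = v/12 for the variance of an arm mean. With time-by-arm terms, the 3-month contrast (A + B)/2 − C has variance w/4 + w/4 + w = 1.5w, against 2w for A − C. The ratio is again 0.75. The factor loses nothing once the time-by-arm terms and the contrast are specified.

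**6. How well can a common A and B mean at 3 months be checked?** The 95% interval for A − B is ± 2.07 × 0.161 = ± 0.33 SD.

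**The case against.** The strongest reply is that a condensed article need not list every contrast. The Abstract says that the model compares the arms over time, so interaction terms may be intended. Aim 1 asks about each program against control and then one program against the other; a pooled lesson effect at 3 months is not a stated objective. That stands in part. The pooled contrast is an efficiency gain that the design allows, and its absence is not an error. But the analysis section does more than stay silent. It writes out the model, names its main fixed effect and its random effect, and assigns time by group to descriptive summaries. A model fitted from that text has the dilution shown above.

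Stronger readings are tempting, and the document does not support them:

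- A reader might infer that coding three arms in itself throws away a quarter of the variance. It does not (step 5). What is missing is the time-by-arm structure.
- A reader might infer that identical treatment will be declared effective in one arm and not in the other, since separate A-versus-C and B-versus-C tests at 3 months would disagree in about 22% of simulated trials if d = .48 in both. The article names no such tests.
- A reader might apply the 25% to the whole study. At 12 months A and B differ and cannot be pooled for the lesson alone.
- A reader might quote B-versus-A power at d = .48. That figure is the pilot effect on intention, used in the sample-size section for an intervention against control. No booster effect size is given.

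**Conclusion.** The point holds as a fault in the stated model for B versus A, together with an unused gain in precision. On the order in the Interventions section, a time-constant arm effect halves the booster effect under equal weighting of the two follow-ups. At assumed correlations of .3 to .7, the booster effect detectable with 80% power is then 0.76 to 0.87 SD, against 0.47 for a plain 12-month contrast. Using the 3-month score as the pre-booster value would improve on 0.47 by an amount that depends on a correlation the article does not give. This needs no Group C data.

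The 25% variance reduction for the lesson effect is exact for equal numbers of sites per arm. It applies only at 3 months and only if Group C is surveyed then, which the timetable and the Retention section put in doubt. If both follow-ups come after the booster, as the effectiveness evaluation section says, A and B are not the same at 3 months and the whole point lapses. The change is worth making before analysis, once those statements agree.

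**What to change.** 1. Reconcile the statements on which groups are surveyed at 3 months (Retention, Table 2, Statistical analysis) and on whether the 3-month survey precedes the booster (Interventions, Intervention effectiveness evaluation).
2. Specify time-by-arm terms, with a child-level random effect or an equivalent within-child correlation in addition to the site intercept.
3. If the 3-month survey precedes the booster, define B versus A as the 12-month contrast with the 3-month score as the pre-booster baseline. Either constrain A and B to a common 3-month mean or enter that score as a covariate.
4. If Group C is also surveyed at 3 months, estimate the lesson effect at that time once, as A and B together versus C, or equivalently as (A + B)/2 − C from the unconstrained model. Show the A and B means separately beside it.

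The cost is a few sentences of model specification. Steps 2 and 3 need no data beyond what is planned for A and B; step 4 needs the Group C survey that the analysis section already describes. The downside is that the constraint assumes children and instructors in Group B do not anticipate the booster. The separate 3-month means can check this only roughly, given an interval of about ± 0.33 SD.

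### The Aim 1 model has a site random intercept only, with no within-child term and no time terms, so standard errors for change over time would be wrong in a direction the plan cannot know

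*Protocol article*

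**What the plan says.** The Statistical analysis section sets the survey times for the primary scale, intention to use hearing conservation strategies: "All individuals will be asked to assess these measures before intervention (baseline), and at 3 months and 12 months after the intervention". It gives two reasons for a mixed model, the cluster design and the fact that "repeated measurements will be collected from the same individuals".

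It then describes the random part of the model: "The random effect in the model is the *site* variable", narrowed to "More precisely, we will use random intercept model for the *site* variable", followed by "We assume the site variable follows a normal distribution with mean zero and is independent to the error terms in the mixed model". Neither this section nor any other names a child-level effect or a covariance among one child's scores.

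The fixed effects named are intervention type and demographic variables. Time and intervention-by-time are absent. Yet the Abstract promises a comparison of the interventions over time, and the Aim 1 text wants to know whether each treatment improved intent more than control did. It assigns that question to descriptive means by time and group, to be examined if the intervention effect is significant, and adds unspecified further tests of one intervention against the other. Under Interventions, the booster is delivered after the 3-month survey.

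**The concern.** The data have three levels: survey wave within child, and child within site. The stated model handles only the site level, although repeated measurement is one of its two reasons for using a mixed model. If the residual errors are the ordinary independent kind, a child's scores are treated as unrelated once site is known.

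This matters most for change. A child's stable level cancels out of a change score, but this model leaves that variance in the residual and charges it to every change contrast. In the other direction, if sites drift differently between waves, a single site intercept cannot represent the drift and the contrast looks more precise than it is. Improvement from baseline is a contrast of this kind. So is the added effect of the booster, which can appear only between 3 and 12 months.

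**Working it through.** **Inputs from the protocol (Power and sample size justification).** 36 sites in three equal arms, so 12 per arm; 16 children per site, so 12 × 16 = 192 per arm; site ICC .10; d = .48; two-sided alpha .05; 80% power.

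**Inputs assumed, because the protocol gives none.** The correlation ρ between two scores of the same child is taken as .3 to .7. The site-by-time variance is taken as 0 or .05. Total variance is 1.

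**The plan's own figure.** Design effect 1 + 15 × .10 = 2.5. Effective size per arm 192/2.5 = 76.8. Noncentrality .48 × √(76.8/2) = 2.974. A t test on 22 df then has 81.1% power, so the stated 80% reproduces. That calculation uses one score per child and does not test the repeated-measures model.

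**Change, with stable site differences.** For the difference between two arms in change between two waves:

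- Site-only model: SE = √(2 × (1 − .10) × 2/192) = √.01875 = .137, whatever ρ is.
- Actual: SE = √(2 × (1 − ρ) × 2/192).

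The type I errors come from 4,000 simulated balanced trials per setting under the null. The power columns use a normal approximation and an illustrative true difference of .25 SD.

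| ρ | Actual SE | Site-only SE | Ratio | Type I error, site-only | Power, child modelled | Power, site-only |
|---|---|---|---|---|---|---|
| .3 | .121 | .137 | 1.13 | 2.6% | 54% | 44% |
| .5 | .102 | .137 | 1.34 | 1.0% | 69% | 43% |
| .7 | .079 | .137 | 1.73 | about 0% | 89% | 41% |

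Adding a child intercept brings type I error back to 4.8% to 5.6%. For a difference in change of .48 SD, power is at least 96% under either model in these settings, so the loss falls on smaller differences.

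**Change, with sites drifting differently.** Split the .10 site variance into .05 stable and .05 wave-specific, with child .45 and error .45. The same-wave ICC is still .10, and ρ = .05 + .45 = .50.

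- Actual: SE = √((2 × .05 + 2 × .45/16) × 2/12) = √(.15625/6) = .161.
- Site-only model, simulated: SE = .138. Ratio .138/.161 = .86, so about 14% too small.
- Simulated type I error: 9% to 10%. With a child intercept added but no site-by-time term, it is about 21%.

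With only a quarter of the site variance wave-specific, the two errors nearly cancel (.133 actual against .137 from the model; type I error about 4.4%).

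**Intervention effect averaged over waves.** With ρ = .5, stable sites and balanced data, the actual SD is .152, the model SE .151 and type I error 5.0%. The site intercept absorbs the extra between-site variance.

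**The case against.** The strongest reply is that the one test the model paragraph names is the intervention effect, and that this test is sound. This stands. In simulation its type I error was 5.4% to 5.5% in balanced data, 4.3% to 5.3% with 20% random dropout, and 5.2% to 5.7% when controls also lacked the 3-month wave. A reader might infer that the main Aim 1 test is invalid or prone to false positives; the documents do not support that. The reply does not settle the matter, because an effect averaged over waves includes the pre-intervention baseline and does not measure improvement.

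Second, the protocol says that the site effect is independent of the errors. It does not say that the errors are independent of each other. A within-child residual covariance would be compatible with that wording and may stand in an analysis plan that is not shown. This also stands: independence within a child is implied by what the text lists, not stated. But the article does spell out the random part and leaves out the level that its own justification names.

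Third, a reader might infer that dropout goes uncorrected because the model cannot use a child's earlier scores. The section on response rate, retention and missing data plans multiple imputation under missing at random with a model based on baseline data, so this point makes no claim about dropout.

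Fourth, three scores per child is not settled for controls. Table 2 has "Distribute, collect 3-month surveys (Groups A,B" only, and the Retention section makes the number of surveys depend on arm. Two scores per child are still correlated, so the point is unchanged.

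**Conclusion.** The point holds for comparisons of change over time and not for the intervention effect averaged over waves. Followed as written with ordinary residual errors, the model gives wrong standard errors for improvement from baseline and for the booster effect after 3 months.

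Size and direction rest on variances the protocol does not give. With stable site differences the error is conservative and costs power. It becomes anti-conservative only if site-by-time variance is large enough, and nothing in the documents shows that it is. A reader might therefore take the model as safely conservative, or as inflating false positives; neither can be claimed from the protocol. The defect does not invalidate the trial, but it should be corrected before analysis.

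**What to change.** In the Statistical analysis section, specify fixed effects for intervention, time and intervention-by-time, alongside the demographic variables already planned. Specify random effects for site, site-by-time and child within site, or site and site-by-time with an unstructured within-child covariance. Use Kenward-Roger or Satterthwaite degrees of freedom for the 36 sites, and drop site-by-time if its variance is estimated as zero. Base the Aim 1 tests on the intervention-by-time contrasts: change from baseline against control, and change after 3 months for the booster. The time terms are essential, since without them the model contains no change contrast. A child intercept alone is not enough, as the 21% figure shows.

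The cost is wording and a slightly more complex model, with some risk of a boundary variance estimate, which the drop rule covers. No further sites, children or surveys are needed for this change.
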